## Protocol Abstract

|                           |                                                                                                                                                                                                                                                                                                                                                                                                                                                                                                                                                                                                                                                                            |
|---------------------------|----------------------------------------------------------------------------------------------------------------------------------------------------------------------------------------------------------------------------------------------------------------------------------------------------------------------------------------------------------------------------------------------------------------------------------------------------------------------------------------------------------------------------------------------------------------------------------------------------------------------------------------------------------------------------|
| Title              | Exploratory Study of SHR-1701 in Combination with Famitinib for the Treatment of Advanced Pancreatic Cancer and Biliary Tract Tumors                                                                                                                                                                                                                                                                                                                                                                                                                                                                                                                                       |

| Study population   | Advanced pancreatic cancer or biliary tract tumors that have failed $\geq 1$ lines of treatment or are intolerant to systemic therapy toxicity                                                                                                                                                                                                                                                                                                                                                                                                                                                                                                                             |
| Study Design       | Single-arm, single-center, Simon's two-stage exploratory study                                                                                                                                                                                                                                                                                                                                                                                                                                                                                                                                                                                                             |
| Number of Subjects | 60                                                                                                                                                                                                                                                                                                                                                                                                                                                                                                                                                                                                                                                                         |
| Objective          | Evaluation of the efficacy and safety of SHR-1701 in combination with famitinib for the treatment of advanced pancreatic cancer and biliary tract tumors                                                                                                                                                                                                                                                                                                                                                                                                                                                                                                                   |
| Endpoint           | 
Primary Endpoint:
 
Objective Response Rate (ORR) based on RECIST 1.1 criteria.
 
Secondary Endpoints:
 
(1) Efficacy Measures:
 

1. Disease Control Rate (DCR) based on RECIST 1.1 criteria.

2. Progression-Free Survival (PFS) based on RECIST 1.1 criteria.

3. Overall Survival (OS).

4. Quality of Life (QoL) assessed using the EORTC QLQ-C30 questionnaire.

 
(2) Safety Measures:
 
Including vital signs, laboratory parameters, Adverse Events (AE), Serious Adverse Events (SAE), drug-related AE and SAE.
 
(3) Biomarker Exploration.
 |
| Procedures         | This study adopts a Simon's two-stage design. Subjects are administered SHR-1701 (30mg/kg, intravenous, once every 3 weeks) in combination with famitinib (20mg, orally, once daily). The initial famitinib dose may be adjusted to 15mg based on the subject's previous treatment tolerance and                                                                                                                                                                                                                                                                                                                                                                           |

current condition. Treatment is administered in cycles of three weeks each, continuously until a treatment termination criterion is met or the subject withdraws from the study. If disease progression per RECIST 1.1 occurs, subjects may continue study treatment at the investigator's discretion if there is potential clinical benefit, acceptable safety, and patient consent.

In Simon Stage I, 15 subjects with pancreatic cancer and 15 subjects with biliary tract tumors are enrolled. If Stage I shows more than 1 case of complete response (CR) or partial response (PR), the study proceeds to Stage II; otherwise, the study is terminated. In Stage II, enrollment continues until reaching approximately 30 subjects, to ensure at least 25 evaluable subjects after accounting for potential drop-out. If there are more than 5 cases of PR or CR in Stage II, the treatment is deemed effective; otherwise, it is considered ineffective.

**Inclusion and  
exclusion criteria**

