**criteria**

- 1) Subject's voluntary withdrawal of informed consent and refusal for further follow-up;
- 2) Other circumstances deemed necessary by the investigator for the subject to withdraw from the study;
- 3) Significant protocol design errors discovered during the conduct of the study;
- 4) Lost to follow-up;
- 5) Subject's death;
- 6) Premature termination of the clinical trial by the sponsor or ethics committee;

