**criteria**

**Efficacy assessment**

Subjects will undergo imaging evaluation every 2 cycles (6 weeks) after enrollment. Tumor response assessment will be performed based on RECIST 1.1 criteria. Subjects with a partial response (PR) or complete response (CR) need to undergo efficacy confirmation 4 weeks later.

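### The success cut-off of more than 5 responses fits 25 subjects per tumour cohort, but enrolment runs to about 30, so the final n and the false-positive rate are left open

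*Protocol*

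**What the plan says.** The Protocol Abstract describes a "Single-arm, single-center, Simon's two-stage exploratory study" with the primary endpoint "Objective Response Rate (ORR) based on RECIST 1.1 criteria". The decision rule is in the Procedures row:

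- **Stage I.** "In Simon Stage I, 15 subjects with pancreatic cancer and 15 subjects with biliary tract tumors are enrolled". The rule to continue reads: "If Stage I shows more than 1 case of complete response (CR) or partial response (PR), the study proceeds to Stage II".
- **Final look.** Enrolment goes on to about 30 subjects, "to ensure at least 25 evaluable subjects after accounting for potential drop-out". The treatment is called effective with more than 5 responses.

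The first look is therefore stated on enrolled subjects and the last is sized on evaluable ones. The document does not define evaluable.

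Three other places bear on the point. Efficacy assessment sets the scan interval: "Subjects will undergo imaging evaluation every 2 cycles (6 weeks) after enrollment". The Study withdrawal criteria list "Subject's death" and loss to follow-up as reasons for leaving the study. Efficacy analysis, under Statistical methods, speaks of estimates for the overall population and names no evaluable-only denominator.

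**The concern.** A Simon cut-off belongs to one sample size. Here the cut-off is a fixed count, while the number of subjects who can contribute to that count may lie anywhere between 25 and about 30. Each further subject is another chance to reach 6 responses. ORR is the only endpoint with a decision rule and there is no control arm, so extra subjects under an unchanged cut-off directly raise the chance of calling an inactive treatment effective.

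A second, conditional issue concerns the reported ORR. With a first scan at 6 weeks in pretreated advanced disease, some subjects may die or withdraw before any post-baseline assessment. If they were classed as drop-outs and left out of the denominator, treatment failures would disappear from the estimate.

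**Working it through.** **Inputs from the protocol (Procedures row):** n1 = 15 per cohort; continue if more than 1 response (r1 = 1); success if more than 5 (r = 5); at least 25 evaluable; about 30 enrolled. The stated total of 60 agrees with 30 in each of two cohorts.

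**Assumptions:**
- Null rate p0 = 10%, target rate p1 = 30%, one-sided alpha 5%, power 80%. The protocol gives none of these.
- The figures 30 and more than 5 are per cohort and cumulative over both stages. The wording that places the 5 responses in Stage II is ambiguous.

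**Step 1: which n does the cut-off fit?** The plan's design cannot be reproduced from its own inputs, since it gives no error rates. An exhaustive search under the assumed values returns exactly 1/15, 5/25 as the minimax design, with alpha 3.28% and power 80.2%. The cut-off thus matches n = 25.

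**Step 2: probability of declaring success.** With X1 ~ Bin(15, p) and X2 ~ Bin(n − 15, p):

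P(success) = Σ over x ≥ 2 of P(X1 = x) · P(X2 ≥ 6 − x)

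At p = 10%:

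| Stage I responses x | P(X1 = x) | P(X2 ≥ 6 − x), n = 25 | Product | P(X2 ≥ 6 − x), n = 30 | Product |
|---|---|---|---|---|---|
| 2 | 0.2669 | 0.0128 | 0.00341 | 0.0556 | 0.01483 |
| 3 | 0.1285 | 0.0702 | 0.00902 | 0.1841 | 0.02365 |
| 4 | 0.0428 | 0.2639 | 0.01130 | 0.4510 | 0.01932 |
| 5 | 0.0105 | 0.6513 | 0.00682 | 0.7941 | 0.00831 |
| 6 or more | 0.0022 | 1 | 0.00225 | 1 | 0.00225 |
| **Sum** | | | **0.0328** | | **0.0684** |

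**Step 3: every final n the text allows, and the next cut-off up.**

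| Final n | Type I error, >5 | Power, >5 | Type I error, >6 | Power, >6 |
|---|---|---|---|---|
| 25 | 3.28% | 80.2% | 0.94% | 65.8% |
| 26 | 3.89% | 83.1% | 1.18% | 70.1% |
| 27 | 4.55% | 85.5% | 1.45% | 74.0% |
| 28 | 5.26% | 87.6% | 1.76% | 77.5% |
| 29 | 6.02% | 89.3% | 2.11% | 80.5% |
| 30 | 6.84% | 90.7% | 2.50% | 83.1% |

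With the cut-off left at more than 5, type I error passes 5% from n = 28.

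**Step 4: range over the unstated null rate.** From n = 25 to n = 30 with more than 5, P(success) goes from 1.2% to 2.7% at p0 = 8%, and from 15.9% to 27.4% at p0 = 15%. The level depends strongly on p0; the increase appears at each value.

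**Step 5: the reported ORR, only if non-assessed subjects are excluded.** Six responses give 6/25 = 24% instead of 6/30 = 20%. A true 10% among 30 (3/30) would read 3/25 = 12% if all 5 excluded subjects were non-responders. The loss of 5 in 30 (16.7%) is inferred from the gap between 30 and 25; the protocol states no drop-out rate.

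**The case against.** Enrolling extra subjects to cover drop-out is routine and does not by itself bias ORR. The analysis set, and the handling of subjects without a post-baseline scan, are commonly left to the SAP, which is not at hand. The study is exploratory and mainly descriptive. All of this stands, and the missing definition of evaluable alone would not justify the point.

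A reader might go further and infer that drop-outs are replaced and removed from the ORR denominator. The protocol says neither. Death as a reason for study withdrawal is an administrative category and does not say that the subject is excluded from ORR. Disease progression is listed under treatment termination, so a subject with documented progression remains assessable.

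A reader might also infer that shrinking the denominator makes the success decision easier. It does not: the decision is a count of responders, and removing non-responders leaves the count unchanged. What raises the error is the number of subjects exposed to a fixed cut-off. For the same reason, Stage I losses confined to non-responders do not make stopping more likely.

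If exactly 25 subjects were evaluable, losses were unrelated to response, and p0 referred to evaluable subjects, the rule would run at its 3.3%. The text does not secure those conditions.

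The mismatch between cut-off and n survives the appeal to the SAP, because the protocol itself fixes the cut-off and the enrolment. A SAP that counted all 30 subjects against the stated cut-off would still give 6.8% under the assumed p0.

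**Conclusion.** The point holds as a mismatch inside the decision rule. The cut-off fits 25 subjects, the text allows any final n from 25 to about 30, and the two looks are stated on different bases. With p0 = 10%, the false-positive rate roughly doubles, from 3.3% to 6.8% per cohort. That result rests on the assumed p0 and on the per-cohort, cumulative reading. The assumed design is not arbitrary, since 1/15, 5/25 is its minimax solution, but the protocol does not confirm it.

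Upward bias in the reported ORR is a possibility that the wording leaves open, not something the protocol prescribes. It should be closed off in the text and not reported as an established error.

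**What to change.** - Base the primary ORR and both Simon decisions on all subjects who received at least one dose, and count those without a post-baseline assessment as non-responders.
- Tie the final cut-off to the actual number treated: 15 treated with more than 1 response to continue; 30 treated with more than 6 for effective (type I error 2.5%, power 83.1% under the assumed rates). If the final n differs from 30, take the cut-off from a table such as the one above, fixed before responses are known. At n = 28, more than 5 gives 5.3% and more than 6 gives 77.5% power, so that n is best avoided.
- State p0, p1, alpha and power, and say that the rule applies per cohort and cumulatively.
- Report evaluable-only ORR as a sensitivity analysis.

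Counting all treated subjects without moving the cut-off would not help: 30 treated with more than 5 is the 6.8% case.

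**Cost.** No subjects are added, but this changes a decision rule and is more than a wording edit. Success becomes stricter: the smallest successful result is 7/30 = 23.3%, and power at n = 30 is 83.1% instead of 90.7% with the looser cut-off, still above the 80.2% of the 25-subject design. The reported ORR will be slightly lower than an evaluable-only figure.

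### The final Simon rule ties the more-than-5 cut-off to responses in Stage II and never says that Stage I responses are carried forward; it should state a cumulative count over both stages, per tumour type

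*Protocol*

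**What the plan says.** The Protocol Abstract describes the trial as a "Single-arm, single-center, Simon's two-stage exploratory study" with "Objective Response Rate (ORR) based on RECIST 1.1 criteria" as the primary endpoint. The decision rule is in the Procedures row:

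- Stage I size: "In Simon Stage I, 15 subjects with pancreatic cancer and 15 subjects with biliary tract tumors are enrolled".
- Stage I boundary: "If Stage I shows more than 1 case of complete response (CR) or partial response (PR), the study proceeds to Stage II".
- Stage II size: "enrollment continues until reaching approximately 30 subjects, to ensure at least 25 evaluable subjects after accounting for potential drop-out".
- Final boundary: "If there are more than 5 cases of PR or CR in Stage II, the treatment is deemed effective"; otherwise the treatment is considered ineffective.

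The total sample size is 60. The document states no null or target response rate, no type I error and no power, and it does not say how Stage I responses enter the final count.

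**The concern.** A Simon design makes its final decision on the cumulative number of responses over both stages. The protocol attaches the final cut-off to Stage II. The Stage I sentence uses the stage name for the subjects of that stage alone, so a reader who treats the final sentence the same way would drop the Stage I responders and ask for at least 6 responses among the subjects added afterwards. There are only 10 to 15 of those per tumour type.

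This rule decides whether the treatment is called effective, and a pre-specified rule should give one verdict from one data set. Take a cohort with 5 responses in Stage I and 5 among 10 new subjects, so 10 of 25, or 40%. The cumulative rule calls it effective and the literal rule calls it ineffective. If the reading is left open, it can be chosen after the results are known.

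**Working it through.** **Inputs from the Protocol Abstract, taken per tumour type**

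- Stage I: 15 subjects; continue with at least 2 responses.
- Final look: at least 25 evaluable, about 30 enrolled; success needs at least 6 responses.
- The figures 30 and 25 are cumulative within a tumour type. Two cohorts of 30 make the stated total of 60, and Stage I alone already enrols 15 + 15 = 30 subjects across both types. Stage II therefore adds 25 − 15 = 10 evaluable subjects, or up to 30 − 15 = 15 if everyone enrolled is evaluable.

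**Assumed, because the document does not give them:** null rate 10%, target rate 30%, one-sided alpha 0.05, power 0.80. Results are shown over a range of true response rates p.

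**Step 1. Which design do the boundaries fit?** With no parameters stated, there is no stated power or alpha to reproduce. An exhaustive search under the assumed values returns 1/15 and 5/25 as the minimax design. Its final cut-off is a cumulative count out of 25.

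**Step 2. Cumulative rule.** With X1 the responses among 15 and X2 the responses among the 10 added:

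P(success) = Σ over x ≥ 2 of P(X1 = x) × P(X2 ≥ 6 − x)

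At p = 0.30:

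| x in Stage I | P(X1 = x) | P(X2 ≥ 6 − x) | Product |
|---|---|---|---|
| 2 | 0.0916 | 0.3504 | 0.0321 |
| 3 | 0.1700 | 0.6172 | 0.1050 |
| 4 | 0.2186 | 0.8507 | 0.1860 |
| 5 | 0.2061 | 0.9718 | 0.2003 |
| 6 or more | 0.2784 | 1 | 0.2784 |

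The products sum to 0.802. The same formula at p = 0.10 gives 0.033.

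**Step 3. Literal rule.** The stages are then two separate hurdles:

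P(success) = P(X1 ≥ 2) × P(X2 ≥ 6)

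At p = 0.30, P(X1 ≥ 2) = 1 − 0.0353 = 0.9647.

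- 10 new subjects: 0.9647 × 0.0473 = 0.046.
- 15 new subjects: 0.9647 × 0.2784 = 0.269.

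**Step 4. Range of true response rates**

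| True ORR | Cumulative, 25 subjects | Literal, 10 new | Literal, 15 new |
|---|---|---|---|
| 10% | 0.033 | 0.0001 | 0.001 |
| 20% | 0.379 | 0.005 | 0.051 |
| 25% | 0.616 | 0.018 | 0.137 |
| 30% | 0.802 | 0.046 | 0.269 |
| 35% | 0.914 | 0.094 | 0.430 |
| 40% | 0.969 | 0.165 | 0.594 |
| 50% | 0.998 | 0.377 | 0.849 |

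**Step 5. Cumulative rule with more than 25 evaluable.** The protocol says at least 25, from about 30 enrolled. If all 30 are counted and the cut-off stays at more than 5, the formula in Step 2 with 15 added subjects gives 0.068 at p = 0.10 and 0.907 at p = 0.30. With 27 evaluable the figure at p = 0.10 is 0.045, and with 28 it is 0.053. The wording of the fix therefore has to deal with the denominator as well as the count.

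**The case against.** The strongest reply is that this is loose wording and not a wrong rule. The protocol does not say that only newly enrolled subjects count, or that Stage I responders are discarded. The sentence just before uses the same phrase cumulatively ("In Stage II, enrollment continues until reaching approximately 30 subjects"), and the design is named as Simon's, whose final boundary is cumulative. The match to a standard 5-of-25 boundary suggests that the authors took a cumulative design and described it imprecisely. The study is also exploratory, its main results are primarily descriptive, and the point estimate and 95% confidence interval of the response rate do not depend on this sentence.

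Most of this stands. Responses by the end of Stage II is the likelier meaning. It does not remove the ambiguity, because the Stage I sentence uses the stage name for that stage alone and nothing in the document says which usage governs the final count. The descriptive analysis reports the response rate but does not settle the effective-or-ineffective verdict that the protocol sets up.

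Two stronger readings are tempting and are not supported. First, a reader might infer that an active regimen would almost always be rejected. That needs the literal reading, only about 10 new evaluable subjects, and a true response rate of about 35% or less. With 15 new subjects the literal rule fails 73% of the time at 30%, 41% at 40% and 15% at 50%. The document sets no target rate, so what counts as active is itself an assumption. Second, a reader might infer that the sponsor designed for 10% versus 30%. The boundaries are consistent with that pair but do not identify it, since neighbouring parameter values can yield the same boundaries.

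**Conclusion.** The concern holds as an ambiguous decision rule whose literal reading is wrong for the named design. If the text is applied literally, the probability of declaring the treatment effective at an assumed true response rate of 30% falls from 0.80 to between 0.05 and 0.27, and at 40% from 0.97 to between 0.17 and 0.59. The lower figure is for 10 new evaluable subjects and the higher for 15.

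These figures assume that the rule is applied separately in each tumour type and that responses are independent with a common rate. The response rates are illustrative, as the document gives none. The documents do not show that the sponsor intends to discard Stage I responses, and the preceding sentence points the other way. The correction is still needed because it concerns a decision threshold, and the two readings disagree on results that could plausibly occur.

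**What to change.** Replace the final sentence of the rule with wording such as: the combination is declared effective in a tumour type if more than 5 of the 25 evaluable subjects from Stages I and II combined in that tumour type have a CR or PR, and ineffective otherwise.

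Two additions belong beside it:

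- **Design parameters.** The sponsor should state the null rate, target rate, type I error and power that it actually used. The 10% and 30% used here are inferred and should not be copied in unless the sponsor confirms them.
- **Denominator.** Either fix in advance which 25 evaluable subjects count (for example, the first 25 in order of enrolment) or adapt the cut-off to the number evaluable. Keeping more than 5 with 30 evaluable subjects raises the type I error at a 10% response rate from 0.033 to 0.068.

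The cost is a short protocol clarification, with no extra subjects, visits or procedures. It should be made before the final responses are known.
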